#### 12.3.5 Visit 5(12 weeks ±5 days, Closing)

1) Measurement of signs of vitality

2) Confirmation of Concomitant medication change

3) Check adverse events

4) Laboratory inspection

5) ECG examination

6) Colposcopic Biopsy test

7) Colposcopy (Reid's Index), Pap smear test

8) HPV DNA test, Hybrid Capture II test

9) NK cell activity, immune phenotype test

It is necessary to confirm the cure or progress of the Cervical intraepithelial neoplasia and to give sufficient medical explanation according to the condition of the Cervical intraepithelial neoplasia of the clinical trial patient and to carry out the follow-up observation or standardized treatment.

## [13] Predictive Side Effects and Precautions for Use

### 13.1 Predictive side effects

No significant adverse events were observed in previous clinical trials of poly gamma glutamic acid, so there is no anticipated side effect, but poly gamma glutamic acid may be a viscous syrup formulation that may cause discomfort when taken according to the individual's taste is predicted.

### 13.2 Precautions for use

Careful administration: No specific side effects have been reported so far, so follow the prescribed dosing instructions. If the patient complains of discomfort or abnormal symptoms during the clinical trial, report to the researcher and the researcher will check whether the adverse reaction has occurred and take appropriate action.

**[14] Clinical Trial Suspension / Dropout Criteria and Analysis Exclusion Criteria**

### 14.1 Clinical Trial suspension ·dropout criteria

The followings are the items which can be the clinical trial stoppage and dropout of the clinical trial patients participating in the clinical trial

1) An acute response (allergic, hypersensitive reaction) to Investigational Product

2) If the investigator determines that continuing participation is not appropriate due to the occurrence of a "serious adverse reaction".

3) In the event of a breach of the selection / exclusion criteria or a violation of a significant clinical study protocol.

4) Patients will be able to withdraw from the trial at their own request.

5) In case of no observation due to absence of clinical test patients.

6) If the other tester determines that the investigator should be stopped.

If the patient is withdrawn from the study, the Investigational Product should be discontinued and the date, reason, and findings should be recorded in the case record, along with all the results of the trial obtained to the point of withdrawal. If a clinical trial is excluded from clinical trials as a result of clinically significant laboratory performance, follow-up should be conducted until the event or laboratory performance is resolved or a reasonable period is determined.

**14.2 Analysis exclusion criteria**

In case of a violation of a critical clinical trial plan, the patient should be excluded from the PP analysis.

1) If the patient's compliance with the Investigational Product is less than 80%

2) In case of violation of selection criteria and exclusion criteria during the test

3) In combination with drugs that may affect the efficacy evaluation

4) When the validity evaluation item inspection (visit 1) is not carried out

5) If you visit due to visiting date

Other violations of the clinical trial protocol, which are considered to have no effect on the interpretation of the study results, must be clearly stated in terms of the violation or delay and the reason and the researcher, sponsor, monitor personnel and statisticians and to include them in the PP analysis.

## [15] Evaluation Criteria, Evaluation Method, and Analysis Method (Statistical Analysis Method)

### 15.1 Effect criteria

The primary and secondary efficacy parameters for evaluating clinical trial results are as follows and the validity will be analyzed for each of the outcome variables.

### 15.1.1 Primary efficacy evaluation variable

The definition of comparative healing between test group and control group at 12 weeks after drug administration compared to Baseline (within -4 weeks) before drug administration means the case of normalization at the level of CIN I.

### 15.1.2 Secondary Validity Variables

Compared to baseline (within -4 weeks) before drug administration Reid Colposcopic Index at 12 weeks after drug administration

Compared to baseline (within -4 weeks) before drug administration Pap smear test results at 12 weeks after drug administration

Comparison of HPV DNA chip test results at 12 weeks after drug administration compared to Baseline (within -4 weeks) before drug administration HPV HC Ⅱ assay results at 12 weeks after drug administration compared to baseline (within -4 weeks)

Comparison of results of NK cell activity at 4, 8 and 12 weeks after drug administration compared to baseline (0 week) before drug administration

(MHC class II) CD8, CD56 population at 4 weeks, 8 weeks, and 12 weeks after administration of drug compared to baseline (0 week) before drug administration.

### Evaluation Method

#### 15.2.1 The primary efficacy end point

Compared to baseline (less than -4 weeks) before drug administration, test group vs. control group at 12 weeks after drug administration

Colposcopic biopsy was performed at visit 1 and visit 5 as a result of colposcopic biopsy, which is a Cervical intraepithelial neoplasia, after drug administration compared to baseline before drug administration. The test group and the control group are compared for the measured healing after 3 months compared with baseline

The stage of change in the Cervical intraepithelial neoplasia of this study is defined as follows.

- Regression: if healed in CIN I

→ Normal in CIN I

- Persistence: if CIN I step is the same without change

→ CIN I to CIN I

- Progression: In case of progressing more than 1 step in CIN I

→ CIN I, CIN II, CIN III, SCC (Squamous cell carcinoma).

#### 15.2.2 The secondary efficacy end point

1) Comparison of Reid Colposcopic Index after administration of drug

Reid Colposcopic Index is a grading system that classifies and scales various findings of CIN lesions according to their characteristics. The score is scored from 0 to 8, and the grading according to the score is determined as follows.

0-2: Likely to be CIN I

3-4: Overlapping lesion - likely to be CIN I or CIN II

5-8: Likely to be CIN II

2) Comparison of Pap smear test results after administration

Cervical cytology was performed using the two-slide technique, using a cytobrush of the uterus and an ectopic cytobrush. The cervical cytology was based on the 2001 Cervical Cytologic Diagnoses. The readings are read in six steps: negative, ASC-US, ASC-H, LSIL, HSIL, and invasive cancer (cervical carcinoma).

3) Comparison of HPV DNA chip test results after administration of drug

Cervical cytology is performed using a specimen collected from uterine and ectopic cytobrush. To confirm the correlation between tumor epithelial cells and HPV infection and virus type. HPV types 16 and 18, 31, 33, 35, 39, 45, 51 and 52 are recorded for positive and negative HPV.

4) Comparison of HPV HC Ⅱ assay results after drug administration

Cervical cytology is performed using a specimen collected from uterine and ectopic cytobrush. It is an examination that is performed as one of the methods to predict the severity of cervical intraepithelial neoplasia. The test result is classified as positive or negative based on the light unit of the sample. If the result is positive, it is recorded as Low, Intermediate, High.

5) Comparison of results of NK cell activity after administration of drug compared to drug administration

Blood is collected from visit 2 and visit 3, visit 4, visit 5, and it is evaluated according to the measurement method of 12.2.8 1).

Recent changes in NK activity measurement using CD107a marker As an ex vivo test, mononuclear cells are first isolated from peripheral blood drawn from subjects. K562 cells are used as target cells of natural killer cells to measure the activity of NK (natural killer) cells. The target cells are inoculated in a FACS tube at a concentration of 4 × 10 5 cells / mL at 100 μL, and peripheral blood mononuclear cells are added to the FACS tube at a ratio of 10: 1 to the target cells. Natural killer cell activity is calculated by measuring the protein labeling on the surface of autologous killing cells when K562 cells, the target cell, are killed

6) Phenotypic changes of peripheral blood mononuclear cells (MHC class II) after drug administration compared with the results of CD8, CD56 population

Blood was collected from Visit 2 and Visit 3, Visit 4, and Visit 5, and evaluated according to the measurement method of 12.2.8 2) Peripheral blood mononuclear cells (PBMNCs) are separated by density gradient method using a boiling solution of ficoll-hypaque after peripheral blood of the subject is collected. Blood samples were superimposed on a Histopaque (specific gravity 1.077 g / ml sterile-filtered, Sigma) solution using a SEPMATE tube (stemcell, 15450) and centrifuged at 1200 xg for 10 min. The upper layer was separated and washed with PBS + 2% To separate mononuclear cells. (PBMNCs) of the subjects were treated with FACS buffer (0.1% Bovine serum albumin, 0.01% sodium chloride) to confirm the change of peripheral blood mononuclear cell immunity phenotype through a flow cytometer (BD-true counter) (CD3-Percp-eFluor 710, CD8-FITC, CD56-PE, CD14-APC-eFluor 780, and CD19-APC-eFluor 780, CD107a-AlexaFluor 647) is added and left on ice for 30 minutes. Fluorescent stained cells were washed twice with FACS buffer, fixed with phosphate buffer containing 2% parafomaldehyde, and then the fluorescence of the cells was measured and analyzed using a flow cytometer (Gallios, Beckman, USA).

###### 15.3 Statistical analysis method

**15.3.1 General principles of analysis**

The purpose of this study was to investigate the effect of oral administration of polygamma glutamic acid (γ-PGA) on the cervical intraepithelial dysplasia (CIN) Phase II clinical studies to confirm. All data obtained in this study are summed up as mean ± standard deviation for continuous data and categorical data for the number of subjects (fraction), and various summary statistics are presented when necessary. If it is necessary to provide an interval estimate, a 95% confidence interval shall be provided.

In the statistical analysis of this data, the first validity criterion, the healing rate, is to be carried out by a one-sided test at a significance level of 5% based on the method of Jung (2008) in the appropriate validity analysis group defined in 15.2. In the analysis other than the primary efficacy evaluation item, the two-sided test is performed at the significance level of 5%. In addition to the efficacy evaluation methods and safety evaluation methods described in 15.3.4 and 15.3.6, when prognostic factors contributing to the outcome variables such as age, perinatal risk, baseline laboratory values, (Eg, logistic model, ANOCOVA, generalized linear model, etc.).

###### 15.3.2 Definition of analytical group

The analytical groups needed to assess efficacy and safety in this trial were performed in both the ITT and PP assay groups as defined below for efficacy assessments in accordance with national and international standards, Define the analysis and evaluate it as a reference.

Efficacy analysis group:

- Intent-to-Treatment (ITT) group: Defined as all subjects assigned to randomization after agreement to participate in the study. But patients who did not take the study drug at least once in the ITT group will be excluded from the analysis group.

- PP (Per Protocol) group: defined as the total subjects who completed the clinical study according to the study plan without any violation of the important research plan presented in 14.2 until the end of the study after the consent to participate in the study.

- In the efficacy evaluation, all the analyzes are performed in the ITT group and the PP group, and the final evaluation is decided according to the results of the ITT group analysis. If the results of the ITT group and the PP group are different, an additional analysis will be conducted exploring why the two analyzes are different.

Safety evaluation analysis group:

After agreeing to participate in the study, they will be defined as the whole subjects who were randomized and who took the research drug at least once.

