### 9.3 Sample size

#### 9.3.1 Sample size

##### - Total 200 patients (PGA Group 100 patients, Placebo Group 100patients)

Based on published literature, we assumed that 31% of the cases of CIN 1 would resolve spontaneously, and a clinically significant difference was estimated at 20%. 80 patients per group.

| Group | Dose | Patient | Expected response Rate | Expected response patient | Duration of treatment/Observation |
| --- | --- | --- | --- | --- | --- |
| Placebo | - | 80 | 31% | 24.8 | administered once daily for 4 weeks /  observation for 8 weeks |
| PGA | 1,500mg/day | 80 | 51% | 40.8 |  |
| Total | - | 160 |  |  |  |

Cervical intraepithelial neoplasia (CIN I) can act as a precursor to invasive cervical cancer and is the most common significant gynecologic disease in women of reproductive age. study, we investigated clinical efficacy and immune response of oral administration of γ-PGA from women with cervical intraepithelial neoplasia 1 (CIN 1) in phase 2b study

H_0_ : p_1_≦p2 vs. H_1_ : p_1_>p_2_

p_1_ : Response rate of treatment, p_2_: Response rate of Control

Expected response rate: PGA Group: 81%, Control Group: 51%

significance level : 0.05, statistical power : 80%, one-sided test

The Sample size is total 160 patients, 80 patients per group when the Single stage method.

If 20% drop out is considered, the sample is total 200 patients, 100 patients per group

The sample size is according to the Two stage optimal design (Jung(2008)) Method is shown in the following table.

[Jung(2008) Two-stage]

| Stage | Patient | Difference between two groups (Treatment patient-Control patient) | 제 significance level, statistical power |
| --- | --- | --- | --- |
| 1  2 | 43  80(43+37) | +2  +11 | 0.461, 0.800 |

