**[11] Study Methodology**

The purpose of this study was to investigate the effect of oral administration of poly-gamma glutamic acid (γ-PGA) on the Cervical Intraepithelial Neoplasia (CIN I) Double-blind, placebo-controlled study designed to identify immunomodulatory effects by assessing changes in immunological parameters.

In this study, a total of 80 patients (100 patients in the case of dropout) were participated in the study. Participation in the study was conducted in two stages as proposed by Jung (2008). In the first stage, 43 subjects were recruited in each group, and the main effect variable, healing, was checked. The difference in the number of subjects in the clinical trial for healing was less than 2 (the number of subjects who were treated for healing of poly-gamma glutamic acid - The number of subjects in clinical trials), it is judged that there is no effect of poly-gamma glutamic acid on cervical epithelial dysplasia and the study is terminated.

If there is more than one difference in step 1, we will consider a two-step study design that will enter step 2 and add an additional 37 patients per group. If the difference in the number of subjects in the clinical trial between group 1 and group 2 of 80 patients in each group is greater than 11 patients, the effect of γ-PGA will be confirmed. Otherwise, γ-PGA. It will be judged that it is not effective in healing the injured Cervical Intraepithelial Neoplasia (CIN I).

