#### 15.3.3 Missing value processing method

In the analysis of validation variables, LOCF (Last Observed Carried Forward) method is applied to replace missing values, and safety evaluation parameters are analyzed without substitution if there is a mistake.

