#### 15.3.4 Analysis of primary efficacy endpoints

In this study, the primary efficacy endpoint was to determine the cure rate as normal at the third month of drug administration of CIN I at baseline as described in 15.2.1 and compare the healing rates between the test and control groups.

The evaluation of the healing rate between the groups was based on the method proposed by Jung (2008). As described above, when 43 patients were selected in each group (intermediate analysis) in the first step, When the difference in number is less than 2 (test group-control group), it is judged that there is no effect of poly gamma glutamic acid, and the present study is terminated. If there were two or more difference in level 1, 37 patients were recruited in each group. In the case of more than 11 patients who were judged to be cured by 80 patients per group, it is judged that there is an effect of poly gamma glutamic acid. If it is less than 11, it is concluded that the effect of poly-gamma-glutamic acid is not ultimately.

If the final number of subjects is different in each analysis group after the end of step 2.

[figure not shown]

here,

n1, n2: Number of subjects per group in steps 1 and 2

a1, a: The first and final stages to determine whether to adopt the null hypothesis. The difference between the groups of healed subjects y1, y2, x1, x2:

b (y|n, p): probability distribution of binomial distribution

We will present the p-value based on the significance level formula.

In addition, the number of children, number of sex partners, and whether smokers are covariates during baseline diagnosis will be analyzed by logistic regression analysis using "exploratory analysis"

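### The +2/+11 decision rule is calibrated for 43 then 80 evaluable patients per group, but the verdict is taken on an ITT set of up to about 100 per group, and the protocol does not say what rule governs there.

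*Protocol*

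**What the plan says.** Section 9.3.1 sets the design: "significance level : 0.05, statistical power : 80%, one-sided test". For the rates, "we assumed that 31% of the cases of CIN 1 would resolve spontaneously, and a clinically significant difference was estimated at 20" (percentage points), which makes 31% against 51%. Its two-stage table gives 43 then 80 (43+37) patients per group, differences of +2 and +11, and an attained level and power printed as 0.461 and 0.800. The same section then says "If 20% drop out is considered, the sample is total 200 patients, 100 patients per group". So 80 is the number expected to remain evaluable and 100 the number randomised.

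Section 15.3.4 words the final criterion as "In the case of more than 11 patients who were judged to be cured by 80 patients per group". It adds that, if the final numbers differ, a formula in the stage sizes and cut-offs (not shown in the text available) yields a p-value that will be presented. Section 15.3.1 requires a one-sided 5% test by the same method.

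Section 15.3.2 defines ITT as all randomised patients except those who never took study drug, and states that "the final evaluation is decided according to the results of the ITT group analysis". Under Section 15.3.3, "LOCF (Last Observed Carried Forward) method is applied to replace missing values". Section 15.2.1 places the biopsy at visits 1 and 5 only. Section 11 describes the first stage as "In the first stage, 43 subjects were recruited in each group", followed by 37 more, and mentions 100 where dropout is allowed for.

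**The concern.** The rule is a difference in counts, so its operating characteristics depend on the number of patients counted. A difference of 11 cures is weaker evidence out of 100 per group than out of 80. LOCF pulls the other way: with biopsies only at screening and week 12, the last observation for a dropout is the qualifying CIN I. Every dropout becomes a failure, both ITT cure rates shrink, and the 20-point difference shrinks with them.

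The quoted level and power therefore belong to a set of patients other than the one that decides the trial. This is the sole primary decision rule and it includes a futility stop. If the cut-off and the recomputed p-value disagree at the actual ITT numbers, nothing says which one settles the conclusion, and the choice could be made after the data are seen.

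**Working it through.** **Inputs.** One-sided 5%, 80% power, 31% v 51%, stage sizes 43 and 37, cut-offs +2 and +11, and 20% dropout (all Section 9.3.1); ITT decides (15.3.2); LOCF (15.3.3); biopsy at visits 1 and 5 (15.2.1).

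**Formula.** Let X1, Y1 be the PGA and placebo cures in stage 1 (n1 per group) and X2, Y2 those added in stage 2 (n2 per group), all independent binomials. The probability of declaring an effect is

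P(X1 − Y1 ≥ 2 and X1 + X2 − Y1 − Y2 ≥ 11),

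computed exactly. With equal rates this is the type I error; with the design rates it is the power.

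**Step 1: reproduce the protocol's figures (43+37).**
- Maximum error over a common rate: 0.0461, at 50%. The printed 0.461 is evidently this number with a misplaced decimal.
- Error at a common 31%: 0.035.
- Power at 51% v 31%: 0.805.
- With ≥12 in place of ≥11: maximum error 0.033, power 0.762.
- At the other rates printed in the section ("Expected response rate: PGA Group: 81%, Control Group: 51" per cent): power 0.989.

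So the design rests on 31% v 51%, on ≥11, and on worst-case error control.

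**Step 2: sizes and rates in the ITT set.** 80/(1 − 0.20) = 100 per group. Stage 1 is either 43 randomised patients (43+57) or 43 completers, 43/0.8 = 53.75, about 54 randomised (54+46). With 20% dropout counted as CIN I, the rates become 0.8 × 51% = 40.8% and 0.8 × 31% = 24.8%.

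**Step 3: unchanged +2/+11 rule at 100 per group.**

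| Quantity | 43+57 | 54+46 |
|---|---|---|
| Maximum error (ITT rate 50%) | 0.061 | 0.065 |
| Error, completer rate 31%, 20% dropout | 0.039 | 0.041 |
| Error, completer rate 38.8%, 20% dropout | 0.048 | 0.051 |
| Error, completer rate 49%, 20% dropout | 0.057 | 0.060 |
| Completer rate at which error passes 5% | 0.405 | 0.38 |
| Power, 20% dropout | 0.763 | 0.785 |
| Power, 15% dropout | 0.800 | 0.822 |
| Power, 10% dropout | 0.833 | 0.854 |

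The 38.8% and 49% rows use natural cure rates cited in Section 9.3.2; the 49% is a six-month figure.

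**Step 4: cut-off that restores 5% at 100 per group.** With ≥2 then ≥12, maximum error is 0.047 (43+57) or 0.0495 (54+46). Power is 0.725 or 0.744 at 20% dropout, and 0.805 or 0.823 at 10%.

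**The case against.** Four points can fairly be made in the protocol's defence.

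1. Section 15.3.4 anticipates differing final numbers. If its p-value, taken at the one-sided 5% of Section 15.3.1, is what decides, the level is preserved. A reader might infer that +11 stays the verdict whatever the ITT size; the text does not say that, because it ties +11 to 80 per group. Equally, it says only that the p-value will be presented, not that it decides. What stands is that the governing criterion is left open.

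2. A reader might infer that the 5% level simply fails. At the protocol's own 31% rate with 20% dropout it does not: the error is about 4%. The worst case needs a 50% ITT rate, which is 0.50/0.80 = 62.5% of completers cured in both groups, above every natural cure rate the protocol cites. But worst-case control is the criterion behind the printed level, and the 5% line is crossed at completer rates of about 38 to 40%, within the range that Section 9.3.2 cites.

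3. The power shortfall at the unchanged cut-off is 1.5 to 4 points, in a trial described as exploratory, and disappears at about 15% dropout or less. That is correct. It does arise at the dropout rate the protocol plans for, and holding 5% as well widens it.

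4. A reader might take the 43 and 37 of Section 11 to mean that only 80 per group are recruited, with no room for dropouts. The section does mention 100 to allow for dropout, so that reading fails. What remains is that 43 and 37 are not labelled as randomised or evaluable.

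**Conclusion.** The point holds in a limited form. The cut-offs, level and power reproduce for 43+37 evaluable patients per group, and the protocol does not say how they carry over to an ITT set of up to about 100 per group with missing biopsies counted as CIN I. Kept unchanged there, worst-case error rises from 0.046 to between 0.061 and 0.065, and power at the planned 20% dropout is 0.763 to 0.785. If 5% is held by recalculation, power is 0.725 to 0.744. On either reading the stated 80% is missed at the planned dropout.

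The documents do not support saying that neither the level nor the power holds in general: the level holds at the planned rate, and the power holds at about 15% dropout or less.

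The figures assume that all 100 per group are dosed, that success means a difference of at least 11 (the reading that reproduces the printed level; Sections 11 and 15.3.4 also speak of more than 11), and that dropout is equal between groups and unrelated to outcome. Equal dropout matters. As an illustration at 54+46 with the unchanged rule, 15% dropout on PGA and 25% on placebo gives an error of 0.108 at a common completer rate of 31%; with those reversed, power is 0.569. Recomputing the cut-off would not cure that.

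**What to change.** - In Sections 9.3.1 and 11, state whether 43 and 37 are randomised or evaluable patients, and give the corresponding randomised stage sizes.
- In Section 15.3.4, make one criterion the verdict: the boundary or p-value from the cited two-stage method, recomputed at the actual ITT stage sizes at one-sided 5%. Say that it replaces the fixed +11 when the numbers are not 43 and 80. As an example, at 54+46 a rule of ≥2 then ≥12 has maximum error 0.0495.
- Use the same inequality for the cut-off throughout, and correct the printed 0.461.
- Restate power for the ITT analysis: about 72 to 74% at 20% dropout and 80 to 82% at 10%.

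The change should be made before the stage 1 analysis. It costs protocol wording and a less favourable power figure, with no added patients. If the sponsor wants 80% power on ITT at 20% dropout, about 117 per group would be needed (stage 1 of 63, +2 then +13: maximum error 0.049, power 0.801); that is optional and not required to repair the rule.
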